### Interventions and cointerventions

In the HSM group, patients will self-administer HSM to treat hypertension. At trial entry, physicians will follow a predetermined standard operating procedure to stimulate the patient for heat-sensitized sensations using round-trip meridian, circling, and sparrow-pecking techniques around any of the acupoints at Yongquan (KI1), Shenque (CV8), and Baihui (GV20) as well as Dazhui (GV14), Quchi (LI11), Hegu (LI4), Taichong (LR3), and Zusanli (ST36). The former three are the main acupoints, and the latter four are the matching acupoints. The patients will select one main acupoint and one matching acupoint with the strongest heat-sensitized sensation as acupoints for HSM self-administration. For bilateral matching acupoints (i.e., Quchi, Zusanli, Hegu, and Taichong), the side with the stronger heat-sensitized sensation will be selected. The administration of HSM at the matching acupoint can be abandoned if all fail to stimulate heat-sensitized sensations.

After acupoint selection, the physicians will explain in detail the technique of HSM to the patients or their families, including how to use the moxibustion jar, ignition, and safety precautions (e.g., preventing burns and smoke evacuation). When dose saturation is achieved (i.e., the heat-sensitized sensations disappear), HSM can be stopped, or the patient can wait until the moxa column has burned completely (approximately 30 min). We will recommend that patients administer HSM once per day at home or at a community healthcare center. Driven by the pragmatic design, we will allow for a lower frequency of HSM when patients are busy, but the procedure must be completed at least two times per week.

Patients in both the HSM and control groups will maintain the use of their original antihypertensive regimen, including antihypertensive drugs or no treatment. The study treatments will last 6 months for all patients. During the trial period, all patients will be prohibited from receiving other acupoint stimulation therapies, such as acupuncture, acupressure, transcutaneous electrical stimulation, or acupoint application therapy. Regular treatment for comorbidities, such as glucose-lowering drugs for patients with diabetes and lipid-lowering drugs for those with dyslipidemia, will be allowed.

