#### Secondary outcomes

A change in mean DBP (mmHg) at month 6 as measured with SBP.The response to treatment at month 6, which is defined as an SBP reduction of ≥ 20 mmHg or DBP reduction of ≥ 10 mmHg for all patients, achieving SBP < 140 mmHg and DBP < 90 mmHg for patients ≥ 65 years or SBP < 130 mmHg and DBP < 80 mmHg for patients < 65 years [17].A change in the mean dosage of the original antihypertensive drug at month 6. At each visit, the physician will decide whether to adjust the original antihypertensive regimen administered to control blood pressure within the ideal range according to the blood pressure measurement, which will be recorded to assess this outcome.A change in mean QoL at month 6, as assessed by the Euro-QoL-5 Dimensions-5 Levels (EQ-5D-5L) questionnaire [19]. This questionnaire includes five items that evaluate QoL in terms of mobility, self-care, usual activities, pain/discomfort, and anxiety/depression. Each item receives a score from 1 to 5 (1, optimal QoL; 5, extremely poor QoL), and a comprehensive index value is calculated from these items, ranging from 0 (extremely poor QoL) to 1 (optimal QoL). The questionnaire also has an overall health status item assessed by a visual analog scale and scored between 0 and 100. A higher score indicates a better overall health status.A change in the mean severity of hypertensive symptoms scored by the symptom scale in the Guiding Principles of Clinical Research on New Drugs of Chinese Medicines at month 6 [20]. The scale assesses 24 hypertension-related symptoms. Each item receives a score of 0 to 3, and a higher score indicates higher severity of that symptom; the total score is the sum of the individual item scores and ranges from 0 to 72 (see details in Additional file 1).Incidence of new-onset cardiovascular events at month 6, including angina, myocardial infarction, and stroke. These data will be collected from patients and family self-reports.Patient compliance with HSM at each visit. This will be determined by the dosage of each administration and the weekly frequency of applications.Cost-effectiveness at month 6, as calculated by comparing the ratio of total treatment cost (China Yuan) to the rate of patients who achieve the targeted response to treatment between the HSM and control groups. Total and antihypertensive treatment costs will be analyzed. Outpatient and inpatient treatment frequencies and costs will also be compared.

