### Recruitment and compliance enhancement

Patients will be invited to participate in the study by their primary care physician at each site. The recruitment advertisement will also be disseminated through posters and the internet. A full understanding of the 6-month follow-up schedule and signing of the informed consent form are prerequisites for participation. Patients’ long-term trust in their physicians is an essential guarantee of their willingness to participate in the study and comply with the protocol. At each visit, patients will obtain a comprehensive health assessment and recommendations for adjusting their medications for hypertension and other diseases. We will also provide a number of rooms with air conditioning and fume extractors at each study site for the patients to administer HSM.

To promote recruitment and compliance, we will provide the patients in both the randomized and nonrandomized HSM groups with two boxes of moxa rolls (108 rolls) per month, which is enough for consumption during the month. At the baseline visit, we will also give the patients two free moxibustion jars, each equipped with a fleece bag that can be slipped over the outside to prevent burns. At the follow-up visits, we will ask the patients to bring the moxibustion jars with them to determine whether the reported frequency of HSM matches the thickness of soot accumulation on the jars. If a moxibustion jar breaks, we will replace it with a new jar. Patients randomized into the control group will receive two more boxes of moxa rolls and two more moxibustion jars than those in the HSM group after completing the study. Because they are not interested in performing HSM, after completing the study, the patients who voluntarily enter the control group will be given a blood pressure monitor that is of equal value to the moxibustion materials.

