### Sample size estimation

The primary purpose of sample size estimation is to meet the need for statistical power for primary outcome comparison between randomized groups. Based on the results of our previous nonrandomized studies (not yet published) and expert opinion, we assume that the SBP in the HSM group will be on average 5 mmHg lower than that in the control group after 6 months of HSM treatment, with a common standard deviation of 8 mmHg between the groups. With a type I error probability “α” of 0.05 and type II error probability “β” of 0.20 and the allowance of a 20% attrition rate, a minimum of 51 patients in either the randomized HSM or control group is needed, as calculated by the following formula for the superiority design [22]:
$$ N=2\times {\left(\frac{Z_{1-\frac{\alpha }{2}}+{Z}_{1-\beta }}{\upmu_1-{\upmu}_2}\right)}^2\times {s}^2 $$

We ultimately decided to enlarge the total sample size to 400, as a sample of this size can be supported by funding. We administered a small preference survey to 100 patients at the study sites, which showed that the ratio of patients with a preference (a strong willingness to enter the HSM or control group) to those without a preference (accept the randomization) was approximately 6:1. Considering the feasibility of the study and the need for confounder adjustment, we established a sample size for the voluntary randomization group of 40 (20 per group) such that the size of the preference selection (nonrandomized) group would be 240 (120 per group). The remaining 120 patients will be entered into the compulsory randomization group (60 per group). Figure 1 illustrates the sample size scheme for each arm.

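### The co-medication rule is stated two ways, and the drug-dose outcome as worded cannot capture antihypertensive changes that may absorb part of an HSM effect

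*Protocol article*

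**What the plan says.** All references are to the protocol article.

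- *Interventions and cointerventions*: "Patients in both the HSM and control groups will maintain the use of their original antihypertensive regimen". The sentence goes on to include patients who take no drug.
- *Secondary outcomes*: at each visit "the physician will decide whether to adjust the original antihypertensive regimen administered to control blood pressure within the ideal range", guided by the pressure measured. The adjustment is recorded in order to assess the outcome defined as "A change in the mean dosage of the original antihypertensive drug at month 6".
- *Recruitment and compliance enhancement*: at each visit patients receive "recommendations for adjusting their medications for hypertension and other diseases".
- *Background*: the add-on comparison is expected to let the investigators observe dosage changes during the study. Whether HSM can replace some antihypertensive dose is listed among the critical questions.
- *Study population*: permitted antihypertensives are calcium channel blockers, angiotensin II receptor blockers, or both.
- *Allocation*: patients and physicians cannot be blinded.
- *Statistical analysis*: the primary outcome is analysed by intention to treat in the full analysis set. Secondary outcomes are assigned a comparison in the per-protocol set. Contamination is the only post-randomization departure named.

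**The concern.** The co-medication statements describe different conduct. If the regimen is held constant, the dose outcome has nothing to measure. If it is adjusted monthly toward a pressure target, the comparison is not HSM added to a constant background. Seven sites need one rule, and an analysis plan cannot supply it, because it governs what physicians do.

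The second half follows from the first. The variable that triggers adjustment is also the primary outcome. When treatment is steered by blood pressure in both arms, a real HSM effect can appear partly as lower SBP and partly as less drug. The SBP comparison then shows only the first part, and the drug outcome must show the second. An outcome restricted to the original drug may miss it. That would weaken the reading of a small SBP difference and would leave the trial's own question about replacing drug dose poorly answered.

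**Working it through.** **1. The co-medication statements side by side.** *Interventions and cointerventions* keeps the original regimen in both arms. *Secondary outcomes* and *Recruitment and compliance enhancement* allow it to change at each visit, and *Background* expects such changes. All of this is current text.

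**2. The dose outcome applied to possible patients.** Taking the definition literally:

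| Patient | Contribution to the outcome as worded |
|---|---|
| On one drug, dose raised or lowered | Counted, but no unit is given that makes doses of two drug classes comparable |
| On one drug, a second drug added | Original dose unchanged, so change = 0 although drug use rose |
| Switched to another drug | Original dose falls to 0, which looks like a reduction |
| Untreated at entry, drug started | No original drug exists, so no value is defined |

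In the last three rows the result is wrong or undefined.

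**3. The analysis set.** *Statistical analysis* names the full analysis set for the primary outcome and the per-protocol set for secondary outcomes. If keeping the original regimen is a protocol requirement, a patient whose regimen changed could count as a deviator and drop out of the comparison of regimen change. The article does not define the per-protocol set, so this is conditional.

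**4. The plan's sample size.** Inputs from *Sample size estimation*: "With a type I error probability “α” of 0.05", two-sided because the printed formula uses Z at 1 − α/2; "type II error probability “β” of 0.20"; SBP "on average 5 mmHg lower than that in the control group after 6 months of HSM treatment"; common SD 8 mmHg; attrition 20%.

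N = 2 × ((1.960 + 0.842)/5)² × 8² = 40.19; 40.19/0.80 = 50.23, rounded up to 51 per arm. The stated figure reproduces; there is no arithmetic error.

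**5. Illustration of dilution.** The documents give no rate of drug adjustment and no drug effect, so both are assumptions. Let x be the excess share of control patients stepped up compared with HSM patients, and e the SBP fall per step.

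Net difference = 5 − x × e.

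Randomized per arm: 60 + 20 = 80; after 20% attrition, 64. Standard error = 8 × √(2/64) = 1.414 mmHg. Two-sided t-test power:

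| x | e (mmHg) | Net difference (mmHg) | Power, 64 per arm |
|---|---|---|---|
| 0 (equal adjustment) | any | 5.0 | 94% |
| 10% | 8 | 4.2 | 84% |
| 20% | 8 | 3.4 | 66% |
| 30% | 8 | 2.6 | 45% |

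The range runs from no loss to a large one, depending wholly on x and e.

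**The case against.** The strongest reply is that maintaining the regimen may only mean that background therapy is not withdrawn at entry, with the outcome section then describing how it may be adjusted. *Background* gives this reading some support. It is plausible, but the text does not say it, and a site reading only the intervention section would not learn that adjustment is allowed. A short clarification is enough.

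A reader might infer that the SBP analysis fails to handle drug changes. The documents do not support that. Intention to treat in a trial described as pragmatic already points to SBP regardless of background drug, which is a legitimate estimate. Further estimates, such as imputing SBP after a drug change, are commonly left to an analysis plan, and that plan is not shown.

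A reader might also infer that added drugs are invisible. That too goes beyond the text: regimen adjustments are recorded, *Visit schedule* records treatment and expenses monthly, and antihypertensive costs are analysed. The data exist; the outcome definition does not use them properly. Nor does the article say that doses are averaged in any particular unit; the unit is simply not given.

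Finally, a reader might infer that the trial is underpowered. The power losses rest entirely on assumed inputs. The 5 mmHg comes from unpublished nonrandomized studies and expert opinion, and it may already be net of drug adjustment. This part of the objection stands in full.

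**Conclusion.** Two things hold. The article states the co-medication rule in conflicting ways, and the passages must be reconciled. The drug outcome, followed as written, gives wrong or undefined values for added, switched and newly started drugs and has no common scale across the two classes, although dose replacement is one of the trial's stated questions. Its assignment to the per-protocol set could make this worse, depending on how that set is defined.

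The primary SBP analysis need not change. It needs a statement of what it estimates and a commitment to read it with drug load. No loss of power is established: the fall from about 94% to 66% requires, for example, a 20-percentage-point excess of step-ups in control and 8 mmHg per step. With equal adjustment in both arms there is no loss.

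**What to change.** 1. Reconcile *Interventions and cointerventions*, *Secondary outcomes* and *Recruitment and compliance enhancement* so that one co-medication rule is stated. Which rule is for the investigators to decide.
2. Redefine the drug outcome as change from baseline to month 6 in total daily antihypertensive load, summed over all antihypertensive drugs in one standard unit, for example multiples of a defined daily dose. Count untreated as 0 and include added, switched and newly started drugs. Compare it in the full analysis set, so that patients whose regimen changed are not removed as deviators.
3. State that month-6 SBP is analysed regardless of drug change, and that SBP and drug load are read together before concluding that HSM has no effect.

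The cost is a clarification of the text and some recoding of regimen data already recorded at each visit. No new data collection and no change in sample size are needed.

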### Outcomes

#### Primary outcome

The primary outcome is a change in mean SBP (mmHg) at month 6, which will be measured using a uniform Omron upper-arm electronic blood pressure monitor at each study site. The measurement will be performed when the patient is in a resting state.

#### Secondary outcomes

A change in mean DBP (mmHg) at month 6 as measured with SBP.The response to treatment at month 6, which is defined as an SBP reduction of ≥ 20 mmHg or DBP reduction of ≥ 10 mmHg for all patients, achieving SBP < 140 mmHg and DBP < 90 mmHg for patients ≥ 65 years or SBP < 130 mmHg and DBP < 80 mmHg for patients < 65 years [17].A change in the mean dosage of the original antihypertensive drug at month 6. At each visit, the physician will decide whether to adjust the original antihypertensive regimen administered to control blood pressure within the ideal range according to the blood pressure measurement, which will be recorded to assess this outcome.A change in mean QoL at month 6, as assessed by the Euro-QoL-5 Dimensions-5 Levels (EQ-5D-5L) questionnaire [19]. This questionnaire includes five items that evaluate QoL in terms of mobility, self-care, usual activities, pain/discomfort, and anxiety/depression. Each item receives a score from 1 to 5 (1, optimal QoL; 5, extremely poor QoL), and a comprehensive index value is calculated from these items, ranging from 0 (extremely poor QoL) to 1 (optimal QoL). The questionnaire also has an overall health status item assessed by a visual analog scale and scored between 0 and 100. A higher score indicates a better overall health status.A change in the mean severity of hypertensive symptoms scored by the symptom scale in the Guiding Principles of Clinical Research on New Drugs of Chinese Medicines at month 6 [20]. The scale assesses 24 hypertension-related symptoms. Each item receives a score of 0 to 3, and a higher score indicates higher severity of that symptom; the total score is the sum of the individual item scores and ranges from 0 to 72 (see details in Additional file 1).Incidence of new-onset cardiovascular events at month 6, including angina, myocardial infarction, and stroke. These data will be collected from patients and family self-reports.Patient compliance with HSM at each visit. This will be determined by the dosage of each administration and the weekly frequency of applications.Cost-effectiveness at month 6, as calculated by comparing the ratio of total treatment cost (China Yuan) to the rate of patients who achieve the targeted response to treatment between the HSM and control groups. Total and antihypertensive treatment costs will be analyzed. Outpatient and inpatient treatment frequencies and costs will also be compared.

#### Safety outcomes

The incidence of any adverse event (AE) and HSM-related AEs will be recorded at each visit. In this trial, an AE is defined as any adverse symptom or occurrence not related to the natural progression of the patient’s original disease. We will record the time, location, course, clinical manifestations, management, and outcome for each AE. The causal relationship between HSM and AEs will be assessed based on five aspects: HSM time and location correlations; whether the AE can be explained by other interventions; reports in previous literature and a plausible biological mechanism; remission or disappearance after HSM discontinuation; and recurrence after HSM resumption [21]. Severe AEs are defined as AEs that are fatal, life-threatening or disabling, or require prolonged hospitalization; these AEs will be immediately reported to the Ethics Committee and the provincial health administration.

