### Data collection and management

At each study site (i.e., community healthcare center), a community physician will be responsible for patient recruitment, HSM training, and outcome assessment; a clinical coordinator will be responsible for regular contact with patients with regard to follow-up visits, recording basic information, and distributing moxibustion materials. Prior to the start of the trial, all investigators will be trained on the standard operating procedure and complete simulated baseline and follow-up visits before being allowed to conduct the investigation.

Raw data will be recorded on paper-based case report forms stored in a lockbox at each study site. Electronic data entry will be performed at any interim analysis and at the end of follow-up by an approach in which two clinical coordinators independently and repeatedly enter the data into standardized forms created in Microsoft Access (Microsoft Corporation, USA). The electronic data set will be anonymized and kept confidential. Only the blinded data analyst can access the data set.

The following trial committees will be established for quality assurance: a steering committee consisting of acupuncturists, cardiologists, methodologists, and statisticians and responsible for study design, maintenance of the quality of study conduct, safety monitoring, and study publication; a coordinating center consisting of the principal coordinating investigator and the coordinating investigators of each community and responsible for the overall study conduct, interactions with the communities and sponsors, and reporting trial advancements to the steering committee; an independent endpoint adjudication committee consisting of cardiologists and acupuncturists and responsible for reviewing the assessment of the primary endpoint and subjective outcomes; and an independent data-monitoring committee consisting of acupuncturists, cardiologists, methodologists, and statisticians for monitoring the data management, directing the interim analysis, and deciding whether to continue the trial based on the results of safety, efficacy, and compliance assessment.

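### Serious events attributed to the natural progression of hypertension can miss the adverse-event comparison and the immediate report, and an admission that is not prolonged need not count as severe

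*Protocol article*

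**What the plan says.** The Safety outcomes section of the protocol article sets out three linked rules.

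- **AE:** defined as "any adverse symptom or occurrence not related to the natural progression" of the patient's original disease. In this trial that disease is primary hypertension.
- **Severe AE:** "Severe AEs are defined as AEs that are fatal, life-threatening or disabling, or require prolonged hospitalization".
- **Immediate report:** "these AEs will be immediately reported to the Ethics Committee and the provincial health administration", where the AEs meant are the severe ones.

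Causality in relation to HSM is then judged for AEs on five aspects.

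Other sections deal with related events. Secondary outcomes lists "Incidence of new-onset cardiovascular events at month 6, including angina, myocardial infarction, and stroke", and adds: "These data will be collected from patients and family self-reports". The Visit schedule section has blood pressure, new disease or disease progression, and AE data recorded at each follow-up visit, as separate items. The Data collection and management section gives an independent data-monitoring committee the task of "deciding whether to continue the trial based on the results of safety, efficacy, and compliance assessment".

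**The concern.** The AE definition builds a judgement about cause into the question of whether an event is an AE at all. In a hypertension trial, the events most easily put down to the underlying disease are those that matter most for safety: stroke, infarction and severe rises in blood pressure. The Background asks whether HSM can replace some doses of antihypertensive drugs, and physicians may adjust the regimen at each visit. Loss of blood pressure control, with its complications, is therefore a foreseeable harm of the strategy under test.

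The Allocation section says that patients and physicians cannot be blinded. Under Data collection and management, the community physician at each site is responsible for recruitment, HSM training and outcome assessment. The article does not name who makes the progression judgement. If it falls to that physician, it is made with knowledge of the arm. A tendency to attribute events to hypertension more readily in one arm than in the other would bias the AE comparison, in a direction that cannot be known in advance.

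**Working it through.** The plan states no figure on this point, so the check is to trace the definitions and set the sections side by side.

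**Step 1: the filter.** An event related to the natural progression of hypertension is not an AE. The Background names hypertension as a leading risk factor for cardiovascular disease and early death, so attributing a stroke or infarction to hypertension is plausible on the article's own terms.

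**Step 2: the subset.** A severe AE must first be an AE. An event removed at step 1 cannot be severe, even if it meets one of the listed criteria ("fatal, life-threatening or disabling, or require prolonged hospitalization").

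**Step 3: the consequences.** An event removed at step 1 is not counted as an AE and has no stated immediate report. It also never reaches the five-aspect causality assessment, since that assessment is applied to AEs.

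**Step 4: the cases.**

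| Event during the trial | AE? | Immediate report stated? | Captured elsewhere? |
|---|---|---|---|
| Disabling stroke, attributed to hypertension | No | No | Yes, secondary outcome and visit record |
| Disabling stroke, not so attributed | Yes | Yes, as severe | Yes, secondary outcome |
| Hypertensive crisis, attributed to hypertension | No | No | Only as disease progression, blood pressure or treatment data |
| Admission for an AE, not prolonged and not fatal, life-threatening or disabling | Yes | No | Yes, inpatient treatment data |

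The first two rows show that the same clinical event is handled differently according to one attribution. The last row is a separate matter: among four criteria for severity, the hospitalisation one mentions only prolonged stays.

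**Step 5: whether the other routes close the gap.**

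- The cardiovascular outcome is assessed at month 6 from patient and family reports. No immediate-report step is attached to it, and hypertensive crisis is not among the events it names. The Study population section nevertheless lists hypertensive crisis and acute cerebral haemorrhage as conditions incompatible with HSM.
- The visit record includes disease progression, but if a visit is missed no follow-up data are collected for that period, and three consecutive missed visits lead to exclusion. A patient who is in hospital or disabled may well miss visits.
- The endpoint adjudication committee reviews the primary endpoint and subjective outcomes. AE classification is not in its stated remit.
- The data-monitoring committee weighs safety, but an AE summary given to it would follow the definition above.

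**The case against.** Much can be said for the plan. Severity does not rest on hospitalisation alone: fatal, life-threatening and disabling events also qualify, so a disabling stroke that counts as an AE is reported at once whatever the length of stay. Angina, infarction and stroke are compared between groups by risk ratio under Statistical analysis, whether or not they are labelled AEs. Blood pressure and disease progression are recorded monthly, the regimen is reviewed at each visit, and inpatient treatment frequencies are compared. The steering committee is responsible for safety monitoring, and an independent committee can stop the trial. The article also calls the cardiovascular events new-onset, and the visit schedule names new-onset disease and disease progression as alternatives. A first stroke could thus be read as new disease, and so as an AE. Finally, an article may leave operational reporting detail to the full protocol.

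Most of this stands, and it rules out three stronger readings that a reader might infer. One is that the severe-AE definition covers only prolonged hospitalisation; it has three further criteria. Another is that strokes and infarctions disappear from the trial; they are counted and compared by arm. The third is that these events are certain to be excluded; the wording makes this possible, not inevitable.

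The objection does not answer the remaining point. Both definitions are given in the article, so this is a rule that is stated and badly fixed, not a detail left to another document. Comparing strokes as an outcome at month 6 does not replace an immediate report of a stroke when it happens. The ambiguity over new-onset events is itself a reason to settle the wording, because unblinded staff would otherwise resolve it case by case.

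**Conclusion.** The point holds in a limited form. As defined, a serious event attributed to the natural progression of hypertension is not an AE, cannot be a severe AE, and has no stated immediate-report route. This depends on an attribution that the article does not protect from knowledge of allocation. Separately, an admission that is not prolonged and meets no other criterion is not severe.

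The harm is confined to AE classification, the by-arm AE comparison and immediate reporting. The secondary cardiovascular comparison and the primary analysis of systolic blood pressure are not affected.

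No number is offered for its size. The documents give neither a rate of such events nor the share that would be attributed to progression, and a count would need both. The conclusion assumes only that hypertension is the original disease meant in the definition and that some serious events would be attributed to it. The change is worth making because it is cheap and concerns participant safety.

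**What to change.** 1. Define an AE as any untoward medical occurrence after entry, regardless of its relation to hypertension or to HSM. Keep the existing five-aspect causality assessment as a separate, later step.
2. Extend the hospitalisation criterion for severe AEs to any admission or the prolongation of one, and leave the other three criteria as they are.
3. State that cardiovascular events collected under Secondary outcomes are also reported as severe AEs when they meet the criteria. Reconcile the Safety outcomes, Secondary outcomes and Visit schedule sections on how disease progression is classified and reported.
4. Compare AEs by arm on the new definition. As recruitment began before this protocol version was dated, apply it also to records already collected, so that one definition holds throughout.

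The cost is the rewording of two definitions, a modest number of extra AE records and ethics committee reports, and a look back through the visit forms for events entered only as disease progression. Sample size, visits and the efficacy analysis are unchanged.
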